### Description of interventions

Instructions for light therapy are equal in both conditions. All participants self-administer light therapy at home for 30 min each morning during a period of 3,5 weeks. Participants start with the light therapy within 30 min after waking up and position the light box at a distance of 45 cm and an angle of 45° from their face. During the light therapy participants can engage in other activities such as reading or having breakfast. They are informed not to stare into the light but to keep their eyes open to ensure that light falls on the retina. No instructions for sleep pattern adjustments are provided in the current trial.

Light therapy in both conditions will be administered via a Litebook© Edge (Litebook, Ltc. Medicine Hat, Canada). The Litebook© Edge is a small (15 × 12 × 1 cm), lightweight box designed to be placed on a table. The Litebook© Edge contains 60 premium white light emitting diode (LED) lights which mimic the visible spectrum of sunlight for minimum glare and maximum eye comfort. For purposes of safety, the Litebook© Edge emits no ultraviolet light. The Litebook© Edge devices used in this study were modified to include an integrated meter that allows for adherence monitoring by recording time and duration of on-time on each day.

#### Intervention group

The intervention group will be exposed to BWL with an intensity of 10.000 lx at a distance of 45 cm. The spectrum of the light in this condition will be enriched around 480 nm wavelengths. Light with this colour has previously been shown to be the effective factor in light therapy as it is associated with melatonin suppression [26].

#### Comparison group

Participants in the comparison condition will be exposed to dim white light, with an intensity of 10–20 lx at a distance of 45 cm. This light was successfully used as a comparison condition for BWL therapy in Alzheimer’s disease. Similar results are expected in cancer survivors [personal communication with [name], November 14, 2016].

### Study procedure

All participants complete a battery of self-report questionnaires and wear a wrist actigraph at four different measurement points (T0: baseline; T1: directly after 3,5 weeks of light therapy; T2: 3 months after light therapy; T3: 9 months after light therapy). The first (T0) and second (T1) measurement points include a visit to the hospital to provide participants with materials and instructions, to perform cognitive tests, and to collect blood (during the visit) and saliva (on day 8 and 36) samples. Figure 2 shows a schematic diagram of a participant’s timeline.

**Fig. 2 Fig2:**
[figure not shown]
Overview of study procedure

The research assistant or study coordinator calls the participant after 5 days of light therapy asking for the occurrence of any side effects (headache, nausea, agitated feeling and irritated eyes). In normal cases, these side effects vanish in a few days. Light therapy is terminated when these side effects are still present after 5 days of light therapy. These participants are asked to complete all follow-up assessments.

After 3,5 weeks of light therapy, participants are asked not to use light therapy during the follow-up measurements. No instructions are provided for the use of concomitant care and other interventions.

### Study measures

#### Sociodemographic and clinical data

Information regarding the patients’ age, education, marital status, living situation, work status and medication use will be obtained via a questionnaire. Clinical information, including date of diagnosis, tumor characteristics, and treatment history will be abstracted from the BETER-database. This clinical information will be abstracted from the patients’ medical record when participants are not included in the BETER-consortium. Current season will be derived from the start date of light therapy.

#### Outcome measures

The Multidimensional Fatigue Inventory (MFI) [41], a VAS-scale for fatigue [42] and the Work and Social Adjustment Scale (WSAS) [43] are the primary outcome measure of this study. Secondary outcome measures include: Pittsburg Sleep Quality Index (PSQI) [44], wrist actigraphy [45], Center for Epidemiological Studies – Depression scale (CES-D) [46], State-Trait Anxiety Inventory-6 items (STAI-6) [47], Medical outcome studies short form (SF-36) [48], Medical Outcomes Studies Cognitive function scale (MOS-CF6) [49], MD Anderson Symptom Inventory (MDASI) [50], Psychomotor Vigilance Task (PVT) [51], 15 words task [52], digit span task [53], cancer worry scale (CWS) [54], fatigue catastrophizing scale (FCS) [55], Self-efficacy scale 28 (SES-28) [56], salivary cortisol and melatonin, and inflammatory biomarkers. Detailed descriptions of these outcome measures are provided in Table 1.

**Table 1 Tab1:** Study outcome measures and corresponding questionnaires

Variable	Questionnaire	Number/type of items	Time frame	Score range	Psychometric details
Primary outcomes					
Cancer related fatigue	MFI [41]	20 four-point Likert scale	Past few days	Subscale scores: 4–20; higher scores indicate more fatigue	Subscales: general fatigue, mental fatigue, physical fatigue, reduced motivation, reduced activity. Cronbach’s alpha: 0.84
	VAS-scale [42]	1 eleven-point Likert scale	This moment	0–10; higher scores indicate more fatigue	
Restrictions caused by fatigue	WSAS [43, 70]	5 nine-point Likert scale	Influence of fatigue on daily life	0–40; higher scores indicate higher levels of disability	Cronbach’s alpha: > 0 .79
Secondary outcomes					
Sleep quality	PSQI [44]	19 four-point Likert scale and open-ended questions	Past month	Total score: 0–21 Subscale scores: 0–3; higher scores indicate more acute sleep disturbances	Subscales: subjective sleep quality, sleep latency, sleep duration, habitual sleep efficiency, sleep disturbances, use of sleeping medication, daytime dysfunction. Cronbach’s alpha: 0.83
Depression	CES-D [46, 71]	20 four-point Likert scale	Past week	0–60; higher scores indicate greater depressive symptoms	Cronbach’s alpha: 0.85–0.90
Anxiety	STAI-6 [47]	6 four-point Likert scale	This moment	20–80; higher scores indicate increased anxiety	Cronbach’s alpha: 0.83
Quality of life	SF-36 [48, 72]	36 Dichotomous three to six-point Likert scale	Past 4 weeks	Subscale scores: 0–100; higher scores indicates higher levels of functioning/well-being	Subscales: physical functioning, role limitations due to physical health problems, bodily pain, social functioning, general mental health, role limitations due to emotional problems, vitality, general health perceptions Cronbach’s alpha: 0.84
Cognitive complaints	MOS-CF6 [49, 73]	6 six-point Likert scale	Past week	0–100; higher scores indicated better cognitive functioning	Cronbach’s alpha: ≥ 0.89
	MDASI [50]	8 eleven-point Likert scale	Past 24 h	0–80; higher score indicates worse or more disturbing cognitive complaints	
Cancer worries	CWS [54]	8 + 1 four-point Likert scale	Past week	9–36; higher score indicates more frequent worries about cancer	Cronbach’s alpha: 0.87
Fatigue catastrophizing	FCS [55, 74]	10 five-point Likert scale	Current attitude	10–40; higher score indicates more catastrophizing	Cronbach’s alpha: 0.85
Self-efficacy	SES-28 [56, 75]	7 four-point Likert scale	Current attitude	7–28; higher score indicates higher level of perceived control over fatigue symptoms	Cronbach’s alpha: 0.68–0.77

*CES-D* Center for Epidemiological Studies – Depression scale, *CWS* Cancer Worry Scale, *FCS* Fatigue catastrophizing Scale, *MDASI* MD Anderson Symptom Inventory, *MFI* Multidimensional Fatigue Inventory**,**
*MOS-CF6* Medical Outcomes Studies Cognitive functioning, *PSQI* Pittsburgh Sleep Quality Index, *SF-36* Medical Outcome Studies short form, *SES-28* Self-efficacy Scale 28, *STAI-6* State Trait Anxiety Inventory-6 items, *VAS* Visual Analogue Scale, *WSAS* Work and Social Adjustment Scale

A brief self-developed questionnaire will be used to examine the use of alcohol and caffeine, screen time prior to sleeping, solarium, wake-up lights, or the use of other interventions that could impact CRF (including physical exercise, CBT, or other interventions). Additional questions assess participant’s experience, compliance, and satisfaction with light therapy. Compliance is also assessed with a light therapy log during light therapy.

#### Actigraphy

Objective measures of sleep and circadian activity will be monitored with an accelerometer in a microelectromechanical system (MotionWatch8, Camntech, Cambridgeshire, United Kingdom). The MotionWatch8 is a small device, similar in size to a watch, with a tri-axial accelerometer. It has a 4.0 Mbits storage capacity and a waterproof casing. This watch will be worn on the non-dominant wrist for 10 (24-h) days at all measurement points and during light therapy. Output of the MotionWatch8 includes the following sleep parameters: time in bed, time out of bed, sleep onset latency (min), sleep efficiency, total time in bed (min), total sleep time (min), wake after sleep onset (min), number of awakenings, and average awakening time (min). Additionally, output of the MotionWatch8 includes the following circadian activity rhythm variables: interdaily stability (IS), Intra-Daily Variability (IV), Least 5 (L5) average, Most 10 (M10) average, and relative amplitude (RA). In addition, it offers nap analyses for naps during the day and day activity analyses.

An actigraphy log will be used to ensure that the scoring software of the actigraph detects the sleep habits of participants accurately. Based on the guidelines for the use of actigraphy, the following items will be included: bed time, attempted time to fall asleep, wake-up time, out-of-bed time, time of day time naps, times the actigraph was removed, unusual circumstances that might have affected sleep/wake patterns (such as illness) [45].

#### Biological samples

##### Salivary cortisol

All participants will be asked to collect saliva to assess cortisol on five different time points during 24 consecutive hours: 1) at personal waking time, 2) 30 min after awakening, 3) 45 min after awakening, 4) at 16.00 o’clock, and 5) at bedtime. These time points are chosen in line with published guidelines for determination of the *Cortisol Awakening Response* (CAR) [57]. The afternoon and evening samples are used to estimate the *diurnal cortisol slope* and the *area under the curve.*

Saliva will be collected by a passive drool technique into a propylene vial. Participants are not allowed to smoke, engage in vigorous exercise, eat or drink caffeinated drinks or food, and eat protein-rich meal during the sampling period starting 1 h prior to sampling. Eating and drinking of other nourishments is allowed until 5 min prior to sampling. Brushing of teeth is not allowed for 30 min before sampling. After sampling, the participant is instructed to record the time that they completed the sample and to refrigerate it. Samples will be returned to the study coordinator by mail after which the samples will be frozen at − 80 °C to keep samples stable until analysis. Cortisol levels will be determined with an electrochemiluminescensce immunoassay ‘ECLIA’ on the Cobas®6000 analyzer (Roche Diagnostics GmbH, Mannheim, Germany).

##### Salivary melatonin

A subgroup (*n* = 25 per condition) will be asked to collect five additional saliva samples in the evening to determine the *Dim Light Melatonin Onset* (DLMO). Starting point for this saliva collection will be 5 h prior to usual bedtime followed by one sample every sequential hour. Previous research indicated that these time points provide a reliable measurement for DLMO with at home collected saliva samples [58]. Participants receive the additional instruction to collect these samples in dim light conditions.

A commercial direct saliva melatonin radioimmunoassay (RIA; Bühlmann laboratories, Schönenbuch, Switzerland) will be used to assess melatonin levels in saliva. The DLMO will be determined based on a threshold of 4.0 pg/mL. Previous research indicated that a fixed threshold is the most convenient way to determine DLMO although there is a risk that DLMO cannot be determined in patients with sleep problems as a consequence of low secretion of melatonin [58]. When we address this problem in the current study, an alternative procedure will be used. DLMO will then be defined as the time when melatonin concentration is two SD above the basal mean of three daytime samples [59].

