There are also several limitations in this trial. First, for practical reasons the duration of light therapy is 3,5 weeks in the current study while previous studies provided light therapy for 4 weeks. Since light therapy for CRF is an upcoming research field, the duration of light therapy and its efficacy is not yet investigated. Clinical practice suggests that the effect of light therapy is often seen within 2 weeks. If no effect is seen in this period, than it is unlikely to see a change in the following weeks. For this reason, it is expected that shortening the time period of light therapy with 4 days will not impact the efficacy of light therapy. Second, a somatic cause for fatigue complaints is an exclusion criterion. Yet, screening does not include assessments of possible somatic factors. Instead, the treating physician judges whether a patient has a somatic cause for fatigue or not. In case of doubt, a team of three experts will be consulted to judge whether someone can be included in the trial. Third, the DLMO is assessed with 5 saliva collections starting 5 h prior to sleep onset. Recommendations by EUCLOCK (a large European wide research network aiming to investigate the circadian clock in single cells and humans) advices to include a saliva collection until 1 h after sleep onset. Yet, this would influence someone’s sleep pattern and might affect fatigue levels the following day. For this reason, saliva is only collected prior to sleep onset.

In conclusion, new insights suggest the efficacy of light therapy as a treatment for cancer related fatigue. If proven to be effective, light therapy will provide an easy to deliver, low-cost and low-burden intervention, introducing a new era in the treatment of CRF. National implementation of light therapy will be facilitated via close collaboration with the BETER-clinics. Moreover, the investigation of potential mechanisms enriches the CRF literature with possible new suggestions for causative factors of CRF, a symptom that is neither well understood nor treated.

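### Melatonin sampling ends one hour before usual bedtime, so onsets after that are right-censored; assaying the existing bedtime saliva would recover most of that gap cheaply

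*Protocol article*

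**What the plan says.** The section Salivary melatonin states that a subgroup of 25 per condition "will be asked to collect five additional saliva samples in the evening to determine the" DLMO. The schedule is: "Starting point for this saliva collection will be 5 h prior to usual bedtime followed by one sample every sequential hour". On light: "Participants receive the additional instruction to collect these samples in dim light conditions".

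The main rule is a fixed cut-off: "The DLMO will be determined based on a threshold of 4.0 pg/mL". The section warns that "there is a risk that DLMO cannot be determined in patients with sleep problems as a consequence of low secretion of melatonin", and gives a fallback: "DLMO will then be defined as the time when melatonin concentration is two SD above the basal mean of three daytime samples". It names no other cause of an undetermined DLMO. It also cites earlier research in support of these time points for home sampling.

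The section Salivary cortisol has all participants give five samples over 24 hours, the last two "4) at 16.00 o’clock, and 5) at bedtime". It mentions no melatonin assay of the bedtime sample. Study procedure places saliva collection on days 8 and 36 and gives no separate day for melatonin.

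The Discussion lists the window as a limitation. It reports a recommendation to sample up to one hour past sleep onset and explains why this was declined: "Yet, this would influence someone’s sleep pattern and might affect fatigue levels the following day". There the five samples are counted back from sleep onset, not from usual bedtime.

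**The concern.** The reason in the Discussion applies to samples taken after a person has gone to sleep. It does not explain why melatonin sampling stops an hour before bedtime, when participants are awake and give a saliva sample at bedtime anyway.

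The values lost are not a random subset: an onset is missing because it comes late relative to bedtime. The fallback changes the threshold but not the window, so it cannot place an onset after the last sample. Because low secretion is the only cause named, the plan has no stated way to handle a participant whose rise simply comes later. Low secretion concerns amplitude; a late rise concerns phase.

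At stake is the secondary objective on the melatonin rhythm and the second mechanism hypothesis in the Background. If BWL moves onset earlier relative to bedtime, fewer onsets are censored at T1 in that arm than under dim white light (DWL), which pulls the observed phase difference toward zero. Statistical analyses relies on mixed models for missing data and provides a correction for non-ignorable dropout. Neither is aimed at a value that is missing because it lies beyond the measurement window.

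**Working it through.** **1. Sampling times.** Inputs from Salivary melatonin: five samples, the first 5 h before usual bedtime, hourly. With time 0 at usual bedtime, t_i = -5 + (i - 1) for i = 1 to 5 gives -5, -4, -3, -2 and -1 h. The last sample is 1 h before usual bedtime and the window is 4 h long. Adding the bedtime vial gives a sixth point at 0 h and a 5 h window. That still ends short of the cited recommendation, which runs to one hour past sleep onset.

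**2. Who is lost.** Sampling is tied to each person's own bedtime. A participant is right-censored only if onset, under the rule in force, falls less than 1 h before bedtime or after it.

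**3. Share affected (assumption).** The documents give no distribution for the onset-to-bedtime interval. Suppose it is normal with mean m and SD s, in hours before bedtime. The share beyond the last sample is Φ((1 - m)/s) now and Φ((0 - m)/s) with a bedtime sample.

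| m (h) | s (h) | Now | With bedtime sample | Of 25, now → then |
|---|---|---|---|---|
| 1.5 | 1.25 | 34.5% | 11.5% | 8.6 → 2.9 |
| 1.5 | 1 | 30.9% | 6.7% | 7.7 → 1.7 |
| 2 | 1 | 15.9% | 2.3% | 4.0 → 0.6 |
| 2.5 | 1 | 6.7% | 0.6% | 1.7 → 0.2 |
| 3 | 0.75 | 0.4% | 0.0% | 0.1 → 0.0 |

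The first and last rows are the extremes over means of 1.5 to 3 h and SDs of 0.75 to 1.25 h.

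**4. Effect on the T1 comparison (illustration).** Assume SD 1 h, mean onset at -2.0 h in DWL and -2.5 h in BWL, so the true difference is 0.5 h. Censoring is then 15.9% against 6.7%, about 4 against 2 of 25. The mean of the observed onsets is μ - φ(c - μ)/Φ(c - μ), where c is the time of the last sample. The few onsets before the first sample (0.1% and 0.6%) are ignored.

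- Now (c = -1): DWL -2.0 - 0.2420/0.8413 = -2.29; BWL -2.5 - 0.1295/0.9332 = -2.64. Difference 0.35 h, so about 30% is lost.
- With the bedtime sample (c = 0): DWL -2.0 - 0.0540/0.9772 = -2.06; BWL -2.5 - 0.0175/0.9938 = -2.52. Difference 0.46 h.

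This is on a bedtime-relative scale. For onset in clock time the loss also depends on how bedtimes vary, which the documents do not give.

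**5. Number of assays.** 25 per condition × 2 conditions × 2 visits (T0 and T1) = 100.

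**The case against.** A reader might infer that participants with a late body clock cannot be measured. The documents do not support that: because the schedule follows each person's own usual bedtime, a late rhythm with an equally late bedtime is covered. Nor do they support the idea that those lost are the people in whom morning light has most room to act.

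A reader might also infer that anyone below 4.0 pg/mL at the last sample has no DLMO. The fallback may rescue some, since a person can pass an individual two-SD threshold while still under the fixed one. And the section does not say that every undetermined DLMO will be classed as low secretion; it only names no other cause.

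The article cites earlier research in favour of these time points. That source is not at hand, and the affected share may be negligible. The limitation is partly disclosed, the measure is exploratory and confined to a subgroup, and the full protocol may say more about use of the samples. Unequal censoring presupposes that onset moves relative to bedtime; no sleep-schedule instructions are given, so bedtime may move too and reduce the imbalance.

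These points limit the size and rank of the concern. They do not supply a reason for leaving out the last waking hour, and neither DLMO rule can place an onset after the last sample.

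**Conclusion.** The point holds in a limited form. The last melatonin sample is 1 h before usual bedtime, so participants with a short onset-to-bedtime interval are right-censored under both DLMO rules, and the stated reason does not cover that hour. How many are affected is an assumption throughout: 0.4% to 34.5% over the range examined, against 0% to 11.5% with a bedtime sample. The shrinkage from 0.5 h to about 0.35 h is an illustration that rests on a normal distribution with SD 1 h and an assumed half-hour advance relative to bedtime; it is not a forecast for this trial.

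The timing anchor also differs between the two sections. If the samples are counted back from sleep onset, as in the Discussion, the last one falls less than 1 h before bedtime for anyone who takes time to fall asleep, and the gap is smaller.

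This is an optional, low-cost improvement to an exploratory subgroup measure. It does not touch the primary outcome.

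**What to change.** 1. In the melatonin subgroup, also assay melatonin in the bedtime saliva sample. State that it is collected on the same evening as the five melatonin samples, extend the dim-light instruction to it, and use its recorded clock time, since actual bedtime may differ from usual bedtime.
2. Analyse a DLMO not reached by the last sample under either rule as later than that sample (right-censored at that person's last sampling time), rather than presuming low secretion. Report the number censored by arm and visit.
3. Reconcile the anchor between Salivary melatonin (usual bedtime) and the Discussion (sleep onset).

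Cost: about 100 extra assays, enough saliva in the bedtime vial for a second assay, and up to one more hour of dim light, which may itself alter evening light exposure slightly. No extra visit and no sampling after sleep onset are needed. The window still ends short of the cited recommendation. Recruitment began in August 2017, so the extra assay may not be possible for everyone; items 2 and 3 need no new samples and can apply to all.

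### The fallback definition of melatonin onset needs three daytime samples that the melatonin schedule does not contain, and the open switch rule allows two onset definitions to be mixed between patients or visits

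*Protocol article*

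**What the plan says.** Under Salivary melatonin, the Protocol article takes a subgroup of 25 per condition who "will be asked to collect five additional saliva samples in the evening to determine the" DLMO. On timing: "Starting point for this saliva collection will be 5 h prior to usual bedtime followed by one sample every sequential hour". The limitations part of the Discussion repeats the count: "the DLMO is assessed with 5 saliva collections starting 5 h prior to sleep onset". It counts from sleep onset rather than usual bedtime, but either way the whole series lies in the hours before sleep. According to Study procedure, saliva is taken at T0 and T1 (days 8 and 36).

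The main definition is a fixed cut-off: "The DLMO will be determined based on a threshold of 4.0 pg/mL". The article then gives its weakness: "there is a risk that DLMO cannot be determined in patients with sleep problems as a consequence of low secretion of melatonin". The remedy is introduced with "When we address this problem in the current study, an alternative procedure will be used", and its content is "DLMO will then be defined as the time when melatonin concentration is two SD above the basal mean of three daytime samples".

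The only other saliva is described under Salivary cortisol: "All participants will be asked to collect saliva to assess cortisol on five different time points during 24 consecutive hours". Those points are waking, 30 and 45 min after waking, 16.00 and bedtime. Cortisol is measured by an electrochemiluminescence immunoassay and melatonin by a radioimmunoassay. Nothing in the article says that a cortisol sample is also assayed for melatonin.

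**The concern.** There are two linked problems.

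First, the fallback rule and the sampling schedule do not fit each other. The rule needs a basal mean and SD from three daytime melatonin values, and the schedule assigned to melatonin contains only evening values. As written, the patients for whom the fallback exists (low secretors) have no designated data from which to compute it.

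Second, if daytime values were found, the rule for moving to the fallback is open. It states no criterion and no unit of application. The stated reason is a problem of individual patients, so the wording allows one patient to be scored by the fixed threshold at T0 and by the basal rule at T1, or patients to be scored differently from one another. The effect of bright against dim light on the melatonin rhythm is a stated secondary objective. What is at stake is whether a T0-T1 difference in DLMO reflects a change in timing or a change in the yardstick.

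**Working it through.** The article states no figure for this point, so there is none to reproduce. The check is a count of samples followed by an illustration of size.

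**1. Samples by time of day.**
- Assigned to melatonin: -5, -4, -3, -2 and -1 h from usual bedtime. That is five evening samples and no daytime samples, against three required.
- Clock times under assumed bedtimes: 21:00 gives 16, 17, 18, 19 and 20 h; 23:00 gives 18 to 22 h; 01:00 gives 20 h to midnight.
- Assigned to cortisol: four samples before the evening (waking, +30 min, +45 min, 16.00) and one at bedtime. Three of the four fall within 45 min of waking.

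**2. Could the first three evening samples stand in?** That leaves 5 - 3 = 2 samples (-2 h and -1 h) in which to detect the rise. The threshold would also be unstable. For independent normal basal values, a further basal sample exceeds mean + 2 SD of three samples with probability P(t with 2 df > 2/√(1 + 1/3)) = P(t > 1.732) = 11.3%. It would be 2.3% if the mean and SD were known. By simulation, at least one of two further basal samples crosses falsely in about 19% of profiles. Simple substitution is therefore not a good repair.

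**3. How far apart are the two definitions?** The article gives no basal levels or rates of rise, so these are assumptions: basal mean 0.5, 1.0 or 1.5 pg/mL with SD 0.2, 0.3 or 0.5, and a linear rise of 2, 4 or 6 pg/mL per h. The fallback threshold is mean + 2 SD, and the difference in onset is (4.0 - fallback threshold) / rise.

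| Basal mean, SD (pg/mL) | Fallback threshold | Rise 2 | Rise 4 | Rise 6 |
|---|---|---|---|---|
| 0.5, 0.2 | 0.9 | 1.55 h | 0.78 h | 0.52 h |
| 1.0, 0.3 | 1.6 | 1.20 h | 0.60 h | 0.40 h |
| 1.5, 0.5 | 2.5 | 0.75 h | 0.38 h | 0.25 h |

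On the same profile the fallback places DLMO 0.25 to 1.55 h earlier. Fallback at T0 and fixed threshold at T1 would look like a delay of that size; the reverse order would look like an advance. The sampling interval is 1 h, so the artefact is of the same order as the resolution of the measurement. A patient who fails to reach 4.0 pg/mL at only one visit has profiles of different height at the two visits, so these figures show the order of magnitude and do not estimate bias.

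**The case against.** The strongest reply is that daytime saliva does exist. The evening samples are additional to the cortisol set, and the cortisol samples are timed, frozen at -80 °C and stored. The Background says that melatonin reaches its lowest point in the morning, so morning saliva is not plainly unfit as a basal level. This stands in part. A reader might infer that the fallback can never be computed, and the documents do not support that. They support a narrower statement: no sample assigned to melatonin is a daytime sample, and reuse of cortisol saliva is nowhere stated. Reuse would be a repair that has to be written down.

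A second reply is that an article leaves tube allocation and trigger rules to the full protocol or SAP. That would excuse silence. Here, however, the article sets out assay, times, threshold and fallback, and the fallback does not fit the times.

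A third reply is that the switch could be meant for the whole study. The sentence that introduces it can be read that way. Switching by patient or visit is permitted by the wording but not announced. A reader might go further and infer that switching would depend on treatment. That is not shown: the stated cause is low secretion, and the article does not say that morning light changes the level of evening secretion.

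The two problems also cannot both bite on the same profile: without daytime values there is no switch, and with them there is no missing input. They are alternative consequences of one unclear rule.

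Finally, a reader might add a power argument. With 25 per arm the detectable difference at 80% power is 0.81 SD, but that follows from the subgroup size and not from the fallback. The article gives no basis for assuming how many patients would lose their DLMO.

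**Conclusion.** The point holds in limited form. The fallback does not match the article's own melatonin schedule (three daytime samples required, none assigned), and the switch rule lets two definitions be mixed across patients or visits. The count rests on the text alone. The possible artefact of 0.25 to 1.55 h rests on the assumed basal levels and rates of rise. How many patients would need the fallback is unknown.

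The scope is a secondary, mechanistic outcome in 50 of 128 participants. The primary fatigue outcomes and their analysis are not affected. The point is worth correcting because the correction is cheap and protects the T0-T1 comparison of DLMO.

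**What to change.** Drop the daytime-sample fallback. Before unblinding, name one DLMO definition that the five evening samples can support: either the 4.0 pg/mL threshold, or one lower fixed threshold above the assay's detection limit, chosen once for the whole subgroup. Apply it to all 50 patients at both T0 and T1. Treat an onset not reached by the last sample as right-censored, and analyse DLMO with a method that accepts censored values. Run any alternative threshold as a sensitivity analysis on every profile, never on selected patients or visits. Choosing the definition patient by patient would not be enough, because it keeps the mixture of definitions.

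The cost is wording in the protocol or SAP, with no new samples or assays. The downside is small: some DLMO values will be censored, with some loss of precision.

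If a daytime baseline is preferred, the plan must name the stored cortisol samples to be assayed for melatonin and apply that rule to all profiles. That means 3 × 2 × 50 = 300 further assays, and at least two of the three samples would come from within 45 min of waking.
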